### Power analysis

2.10.

The power analysis computed the minimally detectable effect size for the aim 1 primary outcome, longitudinal weekly positive saliva drug test response, with the ITT sample after consideration of 10% attrition without completing all 8 post-baseline tests during the trial resulting in *N* = 27 per group. A conservative power analysis is conducted based on this sample size although observations from lost follow-up participants will be included in the primary statistical analysis. With a two-tailed Bonferroni-corrected 0.017 significance level and intra-class correlation coefficient (icc) of the 8 post-baseline repeatedly measured binary outcomes within participants assumed to be less than 0.1, any pairs of the groups (or, especially between TAU and RC + CBT4CBT-Buprenorphine intervention) with >20% outcome difference (e.g., 38% vs. 58%) will be detected with >80% statistical power by the generalized mixed-effects linear models.

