#### Aim 1 analysis plan:

The primary analytic sample will include all randomized participants, referred to as the intention-to-treat (ITT) sample. For the analysis of data from this ITT sample, the group membership will remain unchanged as randomized, even if participants cross over to the other groups during the trial. We will also conduct modified ITT (mITT) analysis, including only participants in the intervention arms who opened at least one CBT4CBT module, and per-protocol (PP) analysis, including those who completed 50% or more modules and/or those who engaged with a RC at least once. To compare the longitudinal primary binary outcome of drug-free test results across the three groups, we will apply generalized mixed-effects linear models to the ITT sample. The primary comparisons will be conducted in pairwise comparisons with a Bonferroni-corrected two-tailed significance level of 0.017 = 0.05/3: 1) RC + CBT4CBT-Buprenorphine vs. CBT4CBT-Buprenorphine; 2) RC + CBT4CBT-Buprenorphine vs. standard of care; and 3) CBT4CBT-Buprenorphine vs. standard of care. As this is an RCT with ITT sample, no adjusting variables will be included in the model. The analysis of secondary outcomes, such as retention in care during the study and follow-up periods, will be similarly conducted.

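### Testing all three pairwise primary comparisons at a fixed 0.017 is valid but gives away power that a step-down test would keep; the stated power is correct but has no reserve above an ICC of about 0.10

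*Protocol article*

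**What the plan says.** Protocol article, section 2.8 (Aim 1 analysis plan): the primary binary outcome, the weekly saliva test result over 8 weeks, is analysed with a mixed model in all randomised participants. All three pairs of arms are compared, each at "a Bonferroni-corrected two-tailed significance level of 0.017 = 0.05/3". No ordering or stepwise rule is given.

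Section 2.10 (Power analysis): the calculation uses 27 per arm after 10% attrition from 30, and the same level ("With a two-tailed Bonferroni-corrected 0.017 significance level"). It also uses an "intra-class correlation coefficient (icc) of the 8 post-baseline repeatedly measured binary outcomes within participants assumed to be less than 0.1". Any pair differing by more than 20 points, for example 38% vs 58%, "will be detected with >80% statistical power by the generalized mixed-effects linear models". The section adds: "A conservative power analysis is conducted based on this sample size", and notes that data from participants lost to follow-up will still be analysed.

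Section 2.1 says that the trial builds on a pilot, OVERCOME I. Section 3 reports that all 90 participants have been randomised and that follow-up was continuing in May 2025. Section 2.8 refers to a separate statistical analysis plan.

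**The concern.** With three arms, the three equality hypotheses are logically linked. If one pair of arms differs, at most one of the other two pairs can be equal. Bonferroni ignores this and holds every comparison at 0.05/3 even after one has been rejected. A trial of 30 per arm has little power to spare, and the comparison that section 1 presents as the unanswered question (coach plus CBT4CBT against CBT4CBT alone) bears the same penalty as the others.

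The second part concerns how the power figure will be read. With 8 tests per person, the ICC decides how much independent information those tests carry. If the assumed ceiling is also the value at which power crosses 80%, the statement has no margin. A reader of a null result may then put more weight on it than the design can bear.

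**Working it through.** **Inputs (section 2.10).** n = 27 per arm, m = 8 tests, two-sided alpha 0.017 (z = 2.387), rates 0.38 and 0.58, ICC below 0.1.

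**1. Reproducing the stated power.** With exchangeable correlation the design effect is 1 + 7 × ICC.
- At ICC 0.10 it is 1.7, so the effective number of tests per arm is 27 × 8 / 1.7 = 216 / 1.7 = 127.1.
- SE = sqrt[(0.38 × 0.62 + 0.58 × 0.42) × 1.7 / 216] = sqrt(0.4792 × 1.7 / 216) = 0.0614.
- Power = Φ(0.20 / 0.0614 − 2.387) = Φ(0.87) = 80.8%.

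With a pooled variance the result is 79.4%, and with a t reference on 52 df it is 78.2%. The ICC at which power is exactly 80% is 0.104 (unpooled) or 0.097 (pooled). The stated figure therefore reproduces, and the assumed ceiling is the break-even point. With all 30 per arm counted, break-even moves only to 0.124.

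**2. Larger ICCs.** The values above 0.1 are assumptions, because the document gives none. The first figure in each range is the pooled method for power and the unpooled method for the detectable difference.

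| ICC | Design effect | Power, 38% vs 58% | Difference from 38% detectable at 80% power |
|---|---|---|---|
| 0.1 | 1.7 | 79-81% | about 20 points |
| 0.2 | 2.4 | 62-64% | 23-24 points |
| 0.3 | 3.1 | 49-51% | 26-27 points |
| 0.5 | 4.5 | 33-35% | 31-32 points |

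Rates further from 50% tolerate more correlation. For 10% vs 30%, power is 95% at ICC 0.1 and 72% at ICC 0.3.

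**3. Why step-down controls the error.**
- All three arms equal: an error needs the smallest p-value to fall below 0.05/3, which has probability at most 3 × 0.05/3 = 0.05.
- Exactly two arms equal: only one null hypothesis is true, and it is never tested above 0.05.
- All arms different: no error is possible.

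Shaffer's thresholds are therefore 0.05/3, then 0.05 and 0.05. Holm's are 0.05/3, 0.025 and 0.05. Neither is ever stricter than 0.05/3, so neither loses a rejection that Bonferroni at 0.05/3 would make.

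**4. Size of the gain.** Simulated beta-binomial data, 27 per arm, 8 tests, t-tests on person means, 40,000 trials per setting.

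| True rates | ICC | Comparison | Bonferroni | Holm | Shaffer |
|---|---|---|---|---|---|
| One arm 20 points from two equal arms | 0.1 | each true difference | 77% | 80% | 84% |
| 38/48/58% | 0.1 | extreme pair | 76.8% | – | 78.4% |
| 30/48/65% | 0.1 | 30% vs 48% | 69% | – | 83% |
| 30/48/65% | 0.3 | 30% vs 48% | 41% | – | 58% |

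Shaffer's simulated familywise error was 4.4-4.7% with all arms equal and about 5% with two arms equal.

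The gain does not make up for a high ICC. At ICC 0.3, with one arm 20 points from two equal arms, Bonferroni gives about 49% and Holm 51-52%. A related closed test (three-group F test at 0.05, then pairs at 0.05) gives about 59%.

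**The case against.** **Multiplicity.** Single-step Bonferroni is a legitimate choice. It controls the error rate and comes with matching simultaneous confidence intervals. The step-down gain is also modest in some settings: under 2 points for the extreme pair at 38/48/58%. The 14-point gain at 30/48/65% comes from a 35-point extreme pair, with which the first step almost always passes. All of this stands, so the point is lost efficiency and not an error.

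**Power.** Four stronger readings are tempting, and the document supports none of them.
- *The power claim is wrong.* It is stated conditionally (ICC below 0.1, difference above 20 points) and it reproduces.
- *The true ICC must exceed 0.1.* Any-drug positivity on a 14-substance panel, in a sample expected to be mostly polysubstance users, may well cluster within persons, but the document contains no estimate. The source of the assumed value may sit in the full protocol or the separate analysis plan. The ICC scale is not stated either. A latent-scale value of 0.10 in a logistic mixed model is about 0.075 on the observed scale, with about 85% power; a latent 0.15 gives about 79%.
- *The label conservative is misplaced.* In section 2.10 it refers to using 27 rather than 30 per arm although partial data will be analysed. That is accurate and says nothing about the ICC.
- *The loss is greatest for coach plus CBT4CBT against CBT4CBT alone.* With equal arms and a common ICC, the loss for a given difference and given rates is the same for every pair.

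Section 5 also presents the trial as preliminary and leaves adequate power to a later trial, which limits the harm from a misread null result.

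**Conclusion.** The point holds as a low-cost improvement. The fixed 0.017 level is valid, but a step-down rule dominates it. In the reference setting (ICC 0.1, one arm 20 points from two equal arms) power per true comparison rises by about 7 points with Shaffer and about 3 with Holm. The gain is larger when all three arms differ widely and very small for the extreme pair under evenly graded effects of 38/48/58%.

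The power statement is correct but has no reserve. For rates near 50% it holds only up to an observed-scale ICC of about 0.10. Whether the trial falls short of 80% cannot be settled from the document. The figures rest on exchangeable within-person correlation, and the power gains also on the beta-binomial model; serial correlation would change the exact values.

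**What to change.** 1. In the analysis plan, before comparative results are seen, replace the fixed level with Shaffer's step-down test: smallest of the three p-values against 0.05/3; if significant, the other two each against 0.05; otherwise stop. Holm is an acceptable alternative with a smaller gain. Use 0.05/3 itself and not the rounded 0.017, since 3 × 0.017 = 0.051.

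2. Keep the power statement and report beside it that the result holds up to an observed-scale ICC of about 0.10 for rates near 50%. Add that under assumed ICCs of 0.2, 0.3 and 0.5, power for 38% vs 58% is about 62-64%, 49-51% and 33-35%, and the detectable difference is about 23-24, 26-27 and 31-32 points. State the ICC scale, and check the value against the OVERCOME I pilot or against pooled data without arm labels. The word conservative can stay.

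Cost: wording and one ICC estimate, with no additional participants. Simultaneous confidence intervals remain at the Bonferroni level, so an interval may include no difference where the step-down test rejects; the report should say so. The power statement will look less favourable.

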## Results

3.

The first enrollment was made in October 2023, and follow-up data collection is still ongoing as of May 2025 although recruitment and randomizations of *N* = 90 participants (*N* = 30 in each arm) have been completed after excluding 2 randomized participants who were identified as ineligible after randomization. The two randomized patients were identified by study coordinators as having insufficient computer skills to receive the web-based CBT4CBT during the study, despite their self-reported adequacy during the screening phase. We determined this as a serious protocol violation and randomly assigned two additional participants to the interventions that were formerly assigned to the two excluded participants who violated the protocol inclusion criteria. The pace of recruitment was approximately five participants per month in a single office-based clinic, suggesting that recruitment of participants from multiple sites across different settings would be necessary for a larger-scale trial.

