### Randomization, concealment, blinding and data management

2.6.

The participants will be randomized in a 1:1:1 ratio with varying masked block sizes to equally distribute *N* = 30 participants to each arm… The random allocation will be concealed, passcode-protected and stored in a secure Research Electronic Data Capture (REDCap) database. Only designated study coordinators will have access to the random allocation code and will dispense upon the availability of patients eligible for enrollment and randomization. Due to the open-label nature of the interventions, it is not feasible to blind the participants or the research coordinators duing assessments conducted at the research visits. However, we will use standardized treatment manuals and protocols to ensure the consistent delivery of the intervention and study assessments across participants, thereby maintaining internal validity of our study and minimizing the risk of potential bias due to the unblinding.

The REDCap database will also be used to collect and manage data, ensuring that all data will be entered into REDCap with no personal identifiers, and source documents will identify participants by study ID. Access to computers used for data entry, management, and analysis will be passwordprotected and limited to the study coordinators. Personal identifying information (including locator information) will be kept in a secure area and a locked file cabinet. More details will be described and specified in a separate data management plan (DMP) document following the HEAL-initiative data ecosystem guidelines. A tentative schematic CONSORT diagram depicting the entire study flow from enrollment steps to the analysis phase is presented in Fig. 1.

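### Two randomised participants were excluded after allocation and their places refilled, so the reported 90 are not the ITT set that the plan defines

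*Protocol article*

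**What the plan says.** Protocol article, Aim 1 analysis plan: "The primary analytic sample will include all randomized participants, referred to as the intention-to-treat (ITT) sample". The same section adds that "the group membership will remain unchanged as randomized, even if participants cross over to the other groups during the trial".

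Protocol article, Results: recruitment and randomisation of 90 participants, 30 per arm, "have been completed after excluding 2 randomized participants who were identified as ineligible after randomization". The two were "identified by study coordinators as having insufficient computer skills to receive the web-based CBT4CBT during the study". The section notes that this came to light "despite their self-reported adequacy during the screening phase". The trial team regarded the matter as a grave breach of protocol. To refill the places, it "randomly assigned two additional participants to the interventions that were formerly assigned to the two excluded participants who violated the protocol inclusion criteria".

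Protocol article, section 2.6: allocation is 1:1:1 in masked blocks of varying size, and it is concealed. "Only designated study coordinators will have access to the random allocation code". Participants and research coordinators cannot be blinded.

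Protocol article, section 2.3: adequate computer skill is an inclusion criterion, to be checked with a literacy survey.

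**The concern.** Three things in the Results do not fit the plan.

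- **The set.** A sample of everyone randomised cannot be one from which two randomised people have been removed.
- **The reason.** The deficit is described as an inability to receive CBT4CBT, which two of the three arms use and usual care does not. It was recognised after allocation by study coordinators in an open-label trial. The same deficit in a usual-care participant is less likely to be noticed or to lead to removal.
- **The replacements.** The two newcomers went to the arms that had been vacated. Those destinations were settled before the newcomers were enrolled, whereas section 2.6 describes concealed blocks.

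What is at stake is comparability of the arms, not power. The Aim 1 plan leaves out all covariate adjustment on the ground that this is a randomised trial with an ITT sample. The primary inference therefore rests on the property that these steps weaken.

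**Working it through.** **Head count.** The Results give 90 after exclusion, with 2 excluded.

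- Ever assigned: 90 + 2 = 92.
- If the replacements are within the 30 per arm, as the text implies, those retained from the planned allocation number 90 - 2 = 88. The 92 are then 88 retained, 2 excluded and 2 replacements.
- Excluded share: 2/92 = 2.2% overall. Within an affected arm it is 1/31 = 3.2% (one in that arm) or 2/32 = 6.3% (both in that arm).

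**The plan's own power figure.** The inputs from section 2.10 are 30 × 0.9 = 27 per arm, 8 tests, ICC below 0.1, 38% versus 58%, and two-sided alpha 0.05/3 ≈ 0.017. The effective number of tests per arm is n × 8/(1 + 7 × ICC).

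- n = 27, ICC 0.10: 216/1.7 = 127.1, power 79.4%.
- n = 27, ICC 0.05: 216/1.35 = 160.0, power 88.9%.

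The stated power above 80% is reproduced to within a point at the ICC limit and exceeded below it. At ICC 0.10, power is 84.1% with 30 per arm and 85.4% with 31. Two participants more or fewer hardly affect power.

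**Possible shift in an arm's positive rate.** Let the arm have 30 participants with positive rate p, and restore k participants who all test negative or all test positive, with equal numbers of tests per person. The new rate lies between 30p/(30 + k) and (30p + k)/(30 + k). The 40% rate is an assumption. The 38% and 58% rates are those of section 2.10.

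| p | k = 1 | shift (points) | k = 2, same arm | shift (points) |
|---|---|---|---|---|
| 40% | 12/31 = 38.7% to 13/31 = 41.9% | -1.3 to +1.9 | 12/32 = 37.5% to 14/32 = 43.75% | -2.5 to +3.75 |
| 38% | 11.4/31 = 36.8% to 12.4/31 = 40.0% | -1.2 to +2.0 | 11.4/32 = 35.6% to 13.4/32 = 41.9% | -2.4 to +3.9 |
| 58% | 17.4/31 = 56.1% to 18.4/31 = 59.4% | -1.9 to +1.4 | 17.4/32 = 54.4% to 19.4/32 = 60.6% | -3.6 to +2.6 |

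The extremes need every test of the restored participants to go the same way.

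**Does the primary model move?** Section 2.9 fits the mixed model to available data. A participant with no post-baseline test contributes nothing to that fit, so 92 and 90 would give the same estimates. The imputation analyses would still change. With missing samples counted as positive, such a participant is positive in all 8 weeks, which is the upper end of the ranges above.

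**Allocation of the replacements.** If the two vacated places were in different arms, chance could at most decide which newcomer took which. If they were in the same arm, chance decided nothing. In neither case could a replacement have been sent to an arm that had not been vacated.

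**What the arms alone could show.** If exclusion were unrelated to arm, both would still fall in the CBT4CBT arms with probability of about (2/3)² = 44%. Finding both there would therefore not by itself prove dependence on arm.

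**The case against.** Computer skill was a prespecified criterion that applied before randomisation. Excluding participants who never met a baseline criterion can be defended when the judgement rests on pre-randomisation information and is made without regard to arm. The event is openly disclosed, concerns 2 of 92, and occurs in a trial that describes its aim as preliminary efficacy. The article announces a separate SAP and does not say outright that the primary model will be fitted to the 90.

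Much of this stands, and it limits the point. A reader might infer that both exclusions came from the CBT4CBT arms only. The article names no arms, and computer difficulties could also surface in usual care, since every participant may have virtual visits and does a computerised task. A reader might also infer that the exclusions favour the intervention. Nothing in the article links low computer skill to more positive tests, and one exclusion in each CBT4CBT arm would tend to cancel in the comparison of those two arms. Nor can one say that chance played no part in placing the replacements.

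The objection does not remove the conflict between the Aim 1 definition and the Results count. The article does not show that the exclusions were judged blind to arm or on pre-randomisation data. It reports that the two passed screening on self-report and were found unsuitable later. Calling the 90 a modified ITT set would not resolve this, because the Aim 1 plan already uses that name for a set based on opening at least one module.

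**Conclusion.** The point holds as a conflict between the definition of the primary analysis set and the count reported. By the plan's own rule the ITT set has 92 members, and 90 is a set formed after exclusion and replacement. The replacements were not allocated by the process in section 2.6.

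Exclusion that depends on arm is a likely risk, not a demonstrated fact, and the sign of any bias is unknown. At an assumed 40% positive rate the bound is -1.3 to +1.9 points for one participant in an arm and -2.5 to +3.75 points for two in the same arm. The larger figure is about a fifth of the 20-point planning difference (3.75/20 = 19%), but it needs both participants in one arm and positive throughout. If the two gave no post-baseline tests, the available-data primary estimates do not change.

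**What to change.** - Make all 92, in the arm allocated, the primary ITT set. Use every saliva test and prescription record available for the excluded pair, and apply the missing-data rules of section 2.9 to the rest.
- Run two sensitivity analyses: one without the two ineligible participants (88 + 2 replacements = 90) and one without the two replacements (88 + 2 excluded = 90). Both have 90 members, but they are different people.
- Report the arm and timing of both exclusions and both replacements in the CONSORT flow.
- Replace the claim that the newcomers were assigned at random with an account of how they were actually allocated.

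The cost is wording in the SAP and the CONSORT flow, plus two refitted models. No new participants are needed. The article reports follow-up still under way in May 2025; the set should be settled before the primary analysis.

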## Discussion

4.

The OVERCOME II study has several innovative features that have not been implemented in any prior studies. First, it will be among the first studies to examine the effectiveness of recovery coaching that will be delivered remotely using computer or smartphone platforms for improving retention to MOUD among individuals with OUD. Although earlier studies explored the impact of incorporating recovery coaching on MOUD initiation rates, this will be the first study to examine the impact of recovery coaching for improving retention among patients already enrolled on MOUD, yet have newly initiated within the past 90 days.

Second, it will also be the first study to test the effectiveness of an intervention combining recovery coaching and CBT4CBT-Buprenorphine in comparison to CBT4CBT-Buprenorphine alone, a comparison that has not been studied. Prior RCTs assessing the effectiveness of recovery coaching for treating SUDs have combined recovery coaching with a variety of therapeutic strategies, including intensive referral interventions, skills training, and multicomponent interventions (involving case management, individual/group treatment, and other services). In addition, the OVERCOME II study is the first RCT examining whether an integrated RC + CBT4CBT-Buprenorphine intervention influences inhibitory control and craving. Thus, we uniquely test whether this integrated intervention can improve substance use recovery by reducing craving and improving inhibitory control over such cravings, which provides a potential mechanism of action for the intervention. This RCT will include novel neurocognitive measures to assess changes in neurocognition such as the Drug Go/NoGo inhibition task with tailored opiate NoGo stimuli and neurocognitive event-related potential (ERP) outcomes.

This study will be the largest RCT (*N* = 90) to examine the effectiveness of web-based CBT4CBT-Buprenorphine intervention for patients on buprenorphine. In addition, the majority of the population will have polysubstance use, including cocaine and methamphetamine use, which reflects the reality of OUD patients being treated in office-based buprenorphine programs. In contrast, the Shi et al. study [28] enrolled 20 patients, and excluded patients with current cocaine, benzodiazepine, and alcohol use disorder.

This study is designed to utilize RCs rather than social workers. RCs assist people with SUDs in navigating various recovery pathways and providing personalized, peer-guided guidance. Unlike social workers, RCs have lived experience with addiction and recovery, which enables them to offer a unique set of comprehensive services that are not part of standard social work practice. In addition, recovery coaches have multiple roles, including advocacy, mentoring/role modeling, social support, instrumental support, motivational interviewing, and assistance in navigating rehabilitation programs. The recovery coach offers the patient with flexibility in developing and formulating a plan that suits their specific needs. Recovery coaches provide lived experience, flexible long-term support, additional areas of support (affiliational and emotional), and work within the community.

Participants in this study may feel burdened by the assessments and visits, which appear to be somewhat lengthy and frequent. To mitigate these potential burdens, we will implement several strategies. First, we will maximize efficiency by combining multiple tasks into a single visit whenever possible (i.e., self-reported and saliva tox assessments). Furthermore, neurocognitive tests will be conducted on separate days. We will schedule research visits to coincide with clinical appointments, thereby minimizing the total number of visits. We will offer convenient scheduling options, including early and evening appointments, as well as remote or hybrid weekly visits via Zoom, making it easier for participants to participate in the study. The therapeutic components, including CBT4CBT and related homework, will be conducted remotely, and patients will complete these activities at their convenience. Participants assigned to the RC + CBT4CBT will be scheduled to meet with the coaches either in person or remotely, based on participant preference, and these meetings will be arranged according to the participant’s availability. Overall, the intervention was designed to be easily integrated into adults’ everyday lives, aiming to minimize burden.

